### Sample size

The sample size calculation was derived from the primary outcomes. Dressings are changed every three days after the first week, and we have used three days as a minimum clinically important difference (MCID) for re-epithelialisation. The standard deviation (SD) on DSW healing, from our database, is four days. We have chosen to power the study to 80%, with an α of 0.05, requiring 28 participants in each group. This sample size is also adequate to determine an MCID of 2 (SD 2.5) in our pain scores using the FLACC and the NRS.

We will use simple randomisation in order to maintain the same degree of DSW dressing unpredictability for each subject. Recruitment will continue until there are at least 28 participants in each arm with primary outcome data. A two-year recruitment period is anticipated, based upon the number of eligible patients requiring grafting in our unit in previous years.

### Data collection

A series of standardised case record forms have been designed using Filemaker Pro 13 (Filemaker Inc., Santa Clara, California, United States). These are loaded onto tablets for use in theatre and in the clinic. These tablets are a standard part of our data collection system already in place, and staff are trained in their use.

Data are collected on baseline demographic and patient condition characteristics, as well as the interventions used. Clinic and operative databases will be married to the study database. Data entry will be by clinic staff in the course of patient treatment. Discrepancies will be resolved by discussion and by re-checking the data. Where consensus is not possible that field will be left empty.

### Data monitoring

Data are monitored weekly for completeness, and reminders are sent to capture incomplete data. All researchers spend a considerable amount of time in the clinic and theatre, and will be closely associated with data collection. We currently capture data on all patients seen in clinic; some of which is submitted to the Australia and New Zealand Bi-national Burns Registry (ANZ Bi-NBR) [27]. The data we collect are more detailed than required for the ANZ Bi-NBR. Our current data completeness rate for our databases is 100%. The dressings we use are already a part of current practice in our unit; therefore we have not set up a data safety monitoring board for adverse effects. Our unit already has a robust monitoring system, with a weekly team meeting and a monthly morbidity meeting.

### Data analysis

All statistical analyses will be conducted using SPSS version 22 (IBM Corporation, Armonk, New York, United States). Demographic data will be analysed through descriptive statistics and between-groups analyses using analysis of variance (ANOVA) and/or non-parametric equivalents where appropriate. Generalised linear models, estimating variance appropriately for repeated measures where required, will be used to determine whether there are differences between groups in primary and secondary outcomes. Changes in the intervention effects will be examined with thickness of split skin graft, donor site surface area and ease of dressing removal considered *a priori* to be of potential interest. All data will be analysed as intention to treat (ITT) and per protocol, with ITT considered the primary method. All tests will be two-tailed and only those with a *P* value <0.05 will be considered statistically significant.

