## Background

Split-thickness skin grafting (STSG) is the most widely used method of achieving skin coverage in burns that are not predicted to heal rapidly with dressings. In harvesting skin to cover the defect, a second wound is created, the donor site wound (DSW). In children, this wound is predicted to re-epithelialise in seven to 14 days. The ideal DSW dressing does not adhere to the wound bed, facilitating removal. DSW dressings should be pain-free, reduce blood loss and be changed infrequently; ideally not until the wound has healed [1-4]. Among clinicians, a pain-free dressing is the most consistently desirable or essential quality of a wound dressing, in recognition of the fact that the DSW is often more painful than the recipient site [5]. The need for such a dressing is, if anything, more important in pediatric burn care as there are data suggesting that decreased pain leads to measurable and clinically significant improvements in wound healing [6-8]. Additionally, rapid healing permits the repeat harvesting of donor areas in larger burns and also decreases the risk of scarring [9].

The optimum dressing for the DSW is unclear, with surgeon and centre choice appearing to follow tradition stemming from eminence as often as it follows selection stemming from evidence. Alginates are the most commonly used DSW dressing [2,3]. There are four systematic reviews investigating DSW dressings [10-13], none of which have identified a single dressing with a clearly superior performance. Data are particularly lacking in pediatric burns, and new dressings are being developed continually. There is a clear need for high quality evidence in pediatric DSW dressings.

Due to the sparse data available, and in recognition of the variety of dressings in our unit, we aim to investigate DSW dressings currently in use in the PLPBC. This trial seeks to answer the following question: in pediatric STSGs, which of the three DSW dressings currently in use at our institution (Algisite™ M, Cuticerin™ and Sorbact®) is superior in terms of pain and itch, wound healing, ease of application and removal, scarring and costs? The best-performing dressing will become our preferred standard, against which we are likely to subsequently repeat the trial as newer dressings become available.

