### Wound treatment

Randomisation occurs immediately before the definitive DSW dressing is applied. Where space between donor sites permits (for example, between the left thigh and right thigh), a second randomisation is permitted. Each wound then constitutes its own study entity and will be analysed separately.

The DSW dressing is taken down in clinic on the seventh post-operative day. Our current standard dressing following this first dressing change is Xeroform® (Covidien, Mansfield Massachusetts, United States) 3% bismuth tribromophenate occlusive petrolatum gauze, which will be applied to all DSWs from this point. We expect the majority of wounds to be healed or nearly healed at seven days, from clinical observation. We have no experience using any of the three study dressings on a DSW beyond this first dressing change.

Clinics occur every weekday, and each patient is seen twice weekly after the first dressing change. This is predicated on ongoing treatment for the grafted site. By reviewing the donor dressing on these occasions we will avoid a requirement for additional clinic visits. Reviewing the dressings every three days after the first week replicates a real-world scenario and means that our results, if positive, will have clinical significance for this outcome.

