#### Secondary endpoints

Itch is a secondary endpoint. The Itch Man Scale will be used for assessing itch. This scale has been validated in children [22]. These assessments will occur at the same time as the pain scores above. Itch will also be assessed at the three, six and 12 month reviews. DSW appearance at three, six and 12 months is a secondary endpoint. This will be assessed in a number of ways: ultrasound measurement of scar thickness; digital three-dimensional photography and edge marking to determine computer-mapped areas of scarring. This will be compared with previous digital images; Patient and Observer Scar Assessment Scale (POSAS) [23]. We chose POSAS as this has superior performance in a systematic review over other scar assessment scales, and from a pragmatic viewpoint is the scale PLPBC staff are most familiar with [24]. It also seeks the opinions of the patient regarding their scar, something we consider important. In practice for many of our young children we use the parent opinion. Where possible we ask both parent and patient. There are some reliability data supporting the use of this scale in children above the age of six years [25]. Below this age caregiver opinion will be sought as a proxy for the child.

Ease of dressing application and removal is a secondary endpoint. Setup time will not be recorded; times for removal and reapplication of dressing will be recorded. A numeric rating scale (0 to four) will be used to ascertain opinions regarding ease of dressing removal at first change. Ease of dressing measurements in theatre are confounded by lack of blinding, and by the variable nature and size of the areas to be dressed. Ease of dressing scores in clinic will focus primarily on the ease with which the primary dressing is removed from the skin surface.

Cost is a secondary endpoint. This will be assessed using hospital pricing for the dressings used, and nursing time for dressing changes. Additional visits, where required, will also be included in the cost analysis. Routine visits will not be costed, since these are a standard part of treatment. Any additional treatments outside of standard care, such as treatment for infection, will be included in costing. A cost-utility analysis will not be performed, as the site and nature of the burn wound grafted will confound quality of life results. We will thus not be able to isolate the DSW from the grafted site in order to perform cost-utility on the DSW alone.

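### Ease of dressing removal, a day-7 outcome of the allocated dressing, is listed with two pre-randomisation factors for examining the treatment effect; used as covariate or modifier, it would make those supplementary analyses non-randomised

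*Protocol article*

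**What the plan says.** All references are to the protocol article.

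- **Data analysis.** Generalised linear models compare the groups on primary and secondary outcomes; no covariates are named in that sentence. The next sentence says "Changes in the intervention effects will be examined with thickness of split skin graft", and its full list reads "thickness of split skin graft, donor site surface area and ease of dressing removal considered". The three are named in advance and on equal footing. Intention to treat is the primary method.
- **Secondary endpoints.** "Ease of dressing application and removal is a secondary endpoint". A 0 to 4 rating "will be used to ascertain opinions regarding ease of dressing removal at first change", and the clinic scores "will focus primarily on the ease with which the primary dressing is removed from the skin surface".
- **Wound treatment.** "Randomisation occurs immediately before the definitive DSW dressing is applied". The first change comes a week later: "The DSW dressing is taken down in clinic on the seventh post-operative day".
- **Surgical procedure.** Graft thickness is measured on a biopsy of the harvested graft, so it is settled when the graft is cut. The wound area is created by the same step.
- **Background.** Easy removal is presented as a property of a good dressing: "The ideal DSW dressing does not adhere to the wound bed, facilitating removal".
- **Primary endpoints.** Pain is scored at four hours, on the next day, just before premedication for dressing removal, and two minutes after removal.

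**The concern.** One variable has two roles. In the endpoint section, ease of removal is something the dressing may change. In the analysis section, it is something by which the dressing's effect is to be examined, next to two quantities the dressing cannot change. The text does not separate them.

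The wording does not say whether the three variables enter as covariates or as interaction or subgroup factors. Either use is a problem for ease of removal:

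- **As a covariate**, it holds constant part of what the dressing does. If a dressing hurts less because it comes off more easily, that part of its benefit is taken out of the adjusted estimate.
- **As a modifier**, it forms strata that treatment itself helps to determine. Children whose dressing came off easily under one product need not be comparable with those whose dressing came off easily under another.

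In both cases, any unmeasured common cause of difficult removal and pain (an anxious child, for example) adds bias even if nothing is mediated. At stake is the interpretation of an analysis that carries the authority of having been named in advance, in a trial meant to choose the centre's preferred dressing.

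**Working it through.** **1. Order of events**

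| Variable | When fixed | Can the dressing affect it? |
|---|---|---|
| Graft thickness | Harvest, before randomisation | No |
| Donor site surface area | Harvest, before randomisation | No |
| Ease of removal | First change, day 7 | Yes; it rates how the allocated dressing comes off |

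**2. Which primary measurements could lie downstream of ease of removal**

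- Pain two minutes after removal: yes, plausibly.
- Pain at four hours, on the next day and before premedication for the first change: no, these precede the removal. Conditioning on a later variable can still bias them, but not by removing a mediated part.
- Healing: unclear. The Wound treatment section expects most wounds to be healed or nearly so at day 7, so ease may reflect healing already achieved.

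**3. The plan's own figures (Sample size section)**

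Inputs: healing difference 3 days, SD 4; pain difference 2, SD 2.5; two-sided α 0.05; power 80%; one pairwise comparison, normal approximation.

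- Healing: n = 2 × (1.960 + 0.842)² × (4/3)² = 27.9, so 28 per group. The stated figure is reproduced.
- Pain: n = 2 × (1.960 + 0.842)² × (2.5/2)² = 24.5, so 25; 28 is adequate, as stated.
- Power for pain at 28 per group: SE = 2.5 × √(2/28) = 0.668; Φ(2/0.668 − 1.96) = Φ(1.03) = 0.85.

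This point does not dispute the sample size.

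**4. Illustration for pain after removal**

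Assumed, not in the documents: a linear model; the dressing shifts ease by one within-arm SD; a share s of the 2-point benefit acts through ease; no other common cause of ease and pain.

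- Adjusted difference = 2 × (1 − s).
- Effect of ease on pain, per SD: b = 2s. Residual SD = √(2.5² − b²).
- Squared correlation of arm and ease, two equal arms: 0.25²/(0.25 × 1.25) = 0.20, so the SE is divided by √0.80 = 0.894.
- Power = Φ(adjusted difference/SE − 1.96).

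| s | Adjusted difference | Residual SD | SE | Power |
|---|---|---|---|---|
| 0% | 2.0 | 2.50 | 0.747 | 0.76 |
| 25% | 1.5 | 2.45 | 0.732 | 0.54 |
| 50% | 1.0 | 2.29 | 0.685 | 0.31 |
| 75% | 0.5 | 2.00 | 0.598 | 0.13 |

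Unadjusted, the difference stays at 2 and power at 0.85 in every row.

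**5. Adding an unmeasured common cause**

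Further assumption: a standardised factor raises ease by 0.5 SD and lowers pain by 1 point. The within-arm slope of pain on ease moves from −2s to −(2s + 0.5), so the adjusted difference becomes 2 − (2s + 0.5) = 1.5, 1.0, 0.5 and 0.0 for the same four shares. Bias is present even at s = 0. If the factor raised pain by 1 point instead, the same arithmetic gives 2 − (2s − 0.5) = 2.5, 2.0, 1.5 and 1.0. The direction is therefore not fixed.

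**The case against.** The strongest reply is that nothing in the plan conditions the primary comparison on ease of removal. The sentence that sets out the group comparison names no covariates; the sentence with the three variables reads as a supplementary exploration. This stands. A reader might infer that a non-adherent dressing's advantage will be adjusted out of the trial's main result, or that the pain analysis will run at about 30% power. The documents do not support that: those figures would apply only if an adjusted model replaced the unadjusted one, and only under an assumed mediated share of one half.

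Further limits also stand. At most one of the four first-dressing pain scores is downstream of removal. The Interventions section's remark on pain and bleeding at removal concerns open weave paraffin gauze, not the study dressings, so a path through wound disturbance is not documented for them. The rater of ease is not named, so scoring by unblinded staff cannot be asserted.

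It can also be said that the sentence might mean a mediation analysis, or that each variable's role belongs in a statistical analysis plan that is not shown. This does not stand. The article describes no mediation analysis. It positively names a post-randomisation outcome as a factor for examining the treatment effect and does not set it apart from two factors fixed at harvest. A later plan that followed the text would carry the problem forward.

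**Conclusion.** The point holds in limited form. Ease of dressing removal does not belong in a list of covariates or effect modifiers with graft thickness and donor site surface area. Used in either way, it gives contrasts that are no longer protected by randomisation. The mechanism of removing part of the effect applies to pain two minutes after removal; elsewhere the bias may take another form or direction.

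The harm shown is to the supplementary analyses and to any adjusted model. Its size cannot be derived from the documents. The range of 2.0 down to 0.5 points rests on the assumed shift in ease, the assumed mediated shares, linearity and the absence of other common causes; step 5 shows how far it moves when the last assumption fails. The timing and double role of the variable are certain from the text; its intended use in the model is not.

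**What to change.** In the Data analysis section:

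1. Remove ease of dressing removal from the variables used to examine changes in the intervention effects. Keep graft thickness and donor site surface area, and state that both are fixed before randomisation.
2. Analyse ease of removal by randomised arm, as the secondary endpoint it already is.
3. If its link with pain after removal is of interest, label that analysis as exploratory mediation, state its assumption of no unmeasured common causes, and say that it does not replace the treatment estimate.

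Cost: one phrase deleted and a sentence or two added. The sample size stays at 28 per group, and no further data or patients are needed.

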### Data storage

Data are backed up to a master file on a University of Queensland server. This file is password protected, and only available to the named researchers on the Human Research Ethics Committee (HREC) approvals. On completion of the project, identifying data will be removed from the record. The record will be kept in perpetuity in order that these data may form a historical cohort if the study is repeated with future dressings. De-identified data may be made available to other researchers in future to facilitate systematic reviews or meta-analyses. If such data are requested, they will only be made available following HREC review and approval.

## Discussion

For such a commonly created wound, it is surprising that there is no uniform dressing choice for DSWs [2,3]. There are a number of possible reasons for this: multiple dressings may have equivalent efficacy; more attention is focused on the grafted site, and the DSW is seen as a secondary priority and there are a lack of reliable and valid data regarding dressing choices.

While there are a number of trials and systematic reviews, heterogeneity between studies makes direct comparisons difficult [10-13]. Tentative recommendations support the use of dressings designed to create a moist healing environment. The majority of studies have been performed in adults. While it is tempting to extrapolate adult data to a pediatric setting this may not be entirely appropriate. Children’s skin is different to adults, and its thickness varies by site, age and gender [28], therefore trials in children may not have the same results as those in adults.

PLPBC DSW dressings are determined largely by surgeon preference and dressing availability on the day of surgery. For external readers this trial will provide data for two dressings against the active control of a calcium alginate. With rigorous trial design, we hope to be able to re-use this protocol in future should additional dressings become available, which may offer advantages over our chosen DSW dressing.

Our trial is intentionally pragmatic; we aim to replicate current clinical practice as closely as possible. We do not, for example, impose additional visits on participants. We are looking for outcomes that are clinically significant, and have chosen endpoints that are important to clinicians, and to patients and their families. Where possible we have used blinded assessments to second-read decisions in clinic. The scales we have chosen have been previously validated in children, and we have experience in all scales that will be used in this trial. This is the first trial of DSW wound healing that incorporates measurement of the harvested graft thickness into the study protocol. This will enable us to correlate healing with donor thickness.

Pain is a primary outcome of interest to parents and clinicians alike, as well as to the patient. Data are mixed on donor site pain, but the majority of studies do agree that DSW pain is often more severe than graft site pain. This is not a surprising finding given the nature of the two wounds. A donor site more painful than its corresponding recipient site has an associated eponym; a positive Moriarty sign is said to be a reassuring sign of impending graft take, rather than graft failure [5].

Time to healing is a relevant primary outcome. Faster re-epithelialisation allows us to re-harvest the donor site, as well as limiting the timespan of this iatrogenic injury. We try where possible to avoid meshed grafts, as the final appearance is cosmetically inferior.

There are a paucity of data on the long-term appearance of a DSW. Much scar studies have focused on the grafted site and DSW scars as well. The Queensland climate is warm, and children often have their thighs uncovered. In our climate the DSW may be more on view than the grafted site itself, as our most common burn injury is a scald to the anterior chest. Scar appearance is a secondary outcome. Scarring is related to the depth of injury, so to accommodate this variable we will be measuring the depth of the STSG at each donor site.

## Trial status

The first patient was randomised intra-operatively on 17 April 2014. As of 1 August 2014 we had recruited 36 patients. A total of 34 have been grafted and randomised to one of the three dressings, with a further two awaiting surgery.

## Abbreviations

ANOVA: Analysis of variance
ANZ BiNBR: Australia and New Zealand Bi-National Burns Registry
CCBTR: Centre for Children’s Burns and Trauma Research
CONSORT: Consolidated standards of reporting trials
DACC: Dialkylcarbamoylchloride
DSW: Donor site wound
FPS-R: Revised Faces Pain Scale
FLACC: Face, Legs, Activity, Cry, Consolability pain scale
HREC: Human research ethics committee
ITT: Intention to treat
MCID: Minimum clinically important difference
NRS: Numeric rating scale
POSAS: Patient and Observer Scar Assessment Scale
RCT: Randomised controlled trial
SD: Standard deviation
PLPBC: Pegg Leditschke Paediatric Burns Centre
SSI: Surgical site infection
STSG: Split-thickness skin graft
TBSA: Total body surface area
